#### Health economic measures

Additionally, cost-effectiveness and cost-utility analyses will be conducted. Data on the cost of interventions will be compared to study outcomes to determine the incremental cost-effectiveness ratio (ICER) of interventions. The ICER is defined as the differential cost of a new treatment and treatment as usual, divided by the outcome differential of the two. Cost-utility analyses will provide information on cost per quality-adjusted life years (QALYs). QALYs are measures combining the additional life years gained by a certain healthcare intervention or program with the quality of life an individual attributes to this lifespan into one single parameter. Thus, QALYs are subjective and universally applicable outcome parameters for comparing health benefits across sectors, disorders, samples or populations. It can be assessed in both patients and healthy individuals. Health-related quality of life will be assessed using the KIDSCREEN-10 [57]. In addition, the health service utilisation of the participants will be assessed by the ‘Mannheimer Modul Ressourcenverbrauch’ (MRV) [63] and transformed into cost estimates for including intervention and treatment as usual costs into the cost-effectiveness and cost-utility analyses of the various study interventions. For transforming health utilisation data, a catalogue of so-called ‘unit costs’ will be compiled for all types of treatments, services or other healthcare measures that were used by study individuals and controls.

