### Data collection

Participants will complete school-based online assessments at time of enrolment in the CP (t_0_) as well as at one and two years after enrolment (t_5_, t_6_) (Fig. 3). SP-specific assessments will be administered following enrolment in the SP (t_1_) and at the SP-specific follow-ups at three (t_2_), six (t_3_) and nine (t_4_) months after enrolment in SP3. All data will be collected online via central servers that are used for both the school-based assessments and the different interventions that are conducted via the ProHEAD online platform. Data will be handled in accordance with German legal regulations concerning data protection and data security (Data Protection Law of the Federal State of Baden-Wuerttemberg, Data Protection Law of the Free and Hanseatic City of Hamburg and German National Data Protection Laws) as well as EU General Data Protection Regulation. Data storage and transfer will be encrypted. All follow-up assessments will be conducted online via a password-secured website and will be recorded in the individual case report forms (CRF). An independent Data and Safety Monitoring Committee (DSMB) will oversee all aspects of data collection, handling and analysis. The DSMB will comprise independent researchers with expertise in research methodology, child and adolescent mental health, and technology-based alcohol interventions. Members of the DSMB will have their first meeting before inclusion of the first study participant.

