
Additional secondary outcomes will be assessed in the school-based follow-ups at one and two years after enrolment. Help-seeking will be assessed using an adapted version of the Actual Help-Seeking Questionnaire (AHSQ) [56], which assesses actual help-seeking behaviour by listing potential help sources and measuring whether help has been sought from the respective sources within a specified time-period for a specified problem. The 13-item questionnaire comprises three subscales: whether informal help has been sought; whether formal help has been sought; and whether no help has been sought. Response options are 0 = ‘no’, 1 = ‘yes, in the past 12 months’ and 2 = ‘yes, but longer ago then 12 months’. The Actual Help-Seeking Questionnaire (AHSQ) is validated in a sample of 16- to 19-year-old students [56]. Mental health symptoms will be assessed using the Strengths and Difficulties Questionnaire (SDQ), a self-report screening questionnaire for children and adolescents aged 2–17 years [42]. The four subscales (emotional, conduct, hyperactivity and peer problems), each scored on a scale of 0–10, will be assessed. Higher scores indicate a higher level of psychopathology. Quality of life will be assessed using the KIDSCREEN-10 [57]. The KIDSCREEN is an international cross-culturally comparable quality-of-life assessment instrument validated for children and adolescents aged 8–18 years. The KIDSCREEN-10 index comprises 10 items, which provide a global measure of health-related quality of life. Items are answered on a 5-point response scale and are coded in a way that higher values indicate better quality of life. Furthermore, program usage patterns (frequency of replies to TIPs, duration, completion) based on log-file data will be analysed.

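### Cost per QALY is promised from KIDSCREEN-10, but the text schedules that instrument only at the one- and two-year school follow-ups, so an early gain that fades within a year could be missed

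*Protocol article*

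**What the plan says.** The protocol article plans two economic analyses under Health economic measures: a cost-effectiveness ratio on study outcomes, and a cost-utility analysis. On the second it says "Cost-utility analyses will provide information on cost per quality-adjusted life years (QALYs"), and on the quality-of-life component "Health-related quality of life will be assessed using the KIDSCREEN-10". No other instrument is named for that purpose, and no time horizon is given.

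Under Secondary outcome measures the instrument is described as a general index: "The KIDSCREEN-10 index comprises 10 items, which provide a global measure of health-related quality of life", with items "coded in a way that higher values indicate better quality of life". The block that contains this description opens with "Additional secondary outcomes will be assessed in the school-based follow-ups at one and two years after enrolment".

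Data collection sets out two series of assessments. The central project has "school-based online assessments at time of enrolment in the CP (t_0_) as well as at one and two years after enrolment" (t5 and t6). The trial (sub-project SP3) has its own assessment at sub-project enrolment (t1) and follow-ups at three, six and nine months after that enrolment (t2 to t4). The Design section confirms that the two series count from different starting points.

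**The concern.** A QALY difference is the area between the arms' utility curves over time, so it can only reflect what happens between measurements if the measurements are close enough together. Prompts run for 12 weeks and the primary outcome is read at nine months, so any benefit to quality of life may well be largest in the first months and fade afterwards. The text places no quality-of-life measurement for the QALY at t1 to t4, the assessments timed from randomisation. It gives only later points, timed from an earlier event.

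At stake is the cost-utility result. The article wants QALYs so that health benefits can be compared across sectors and populations, and its Discussion presents the trial as the first to examine cost-effectiveness of such booster messages. A utility conversion can be chosen after the data are in. Values not collected at t1 to t4 cannot be recovered by any later analysis.

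**Working it through.** The article states no QALY figure, utility value or horizon, so there is nothing to reproduce. The check has three steps.

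**1. Where the text places the instrument.** The secondary-outcome text assigns the brief RAPI to the sub-project follow-ups and puts KIDSCREEN-10 in the one- and two-year school block. Health economic measures names KIDSCREEN-10 again without timing. Nothing in the text places it at t1, t2, t3 or t4. Nor does the text say outright that it is given at the school baseline (t0).

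**2. The two clocks.** Let L be the months from central-project enrolment (t0) to SP3 enrolment (t1). L is not given. The one-year school assessment then falls 12 − L months after SP3 enrolment.
- L = 0: month 12.
- L below 3: after the nine-month endpoint.
- L of 3 or more: at or before the nine-month endpoint, at a time that can differ between participants.

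**3. What interpolation recovers.** Assumptions, none of them from the document: L = 0; a utility scale is available; the arms do not differ at month 0; u is the utility difference between two arms; values are known only at months 0, 12 and 24 and are joined by straight lines (trapezoid rule).

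| Assumed course of the gain | True area (QALY) | Trapezoid | Lost |
|---|---|---|---|
| u to month 9, then linear to 0 at month 12 | (9 + 3/2)/12 u = 0.875u | (0 + 0)/2 × 1 = 0 | 100% |
| u throughout, 12-month horizon | 12/12 u = 1.0u | (0 + u)/2 × 1 = 0.5u | 50% |
| u throughout, 24-month horizon | 24/12 u = 2.0u | 0.5u + 1.0u = 1.5u | 25% |
| linear rise from 0 to u at month 12 | 0.5u | 0.5u | 0% |
| 0 to month 9, then u to month 12 | 3/12 u = 0.25u | 0.5u | none; overstated by 0.25u |

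The first row is the case that matters for a 12-week booster whose effect fades within the year.

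**The same case with t1 to t4 added.** The observed differences at months 0, 3, 6, 9 and 12 are 0, u, u, u, 0. The trapezoid sum is 3/12 × (0.5u + u + u + 0.5u) = 0.75u. The loss falls from 0.875u to 0.875u − 0.75u = 0.125u, and 0.125/0.875 is about 14%.

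**The case against.** The strongest reply is that the schedule by instrument sits in Fig. 3, which cannot be seen here. Its legend lists KIDSCREEN-10 together with central-project and trial measures, so the figure could show it at t1 to t4. That stands, and it limits the point to what the text says.

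Several stronger inferences are tempting, and the document does not support them:

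- *That QALYs cannot be derived at all.* No horizon is set, and follow-up at one and two years is part of the design. QALYs over those periods remain possible once a conversion is fixed. An article may leave the conversion to the full protocol or a health-economic plan, so its absence here is not in itself a fault. Nor does the article say that the raw score will serve as the utility.
- *That no quality-of-life value falls within nine months of randomisation.* With L of 3 months or more, the one-year school assessment would fall inside that window.
- *That the trial sample receives the SCL-K-9 in place of KIDSCREEN-10.* Further measures introduces the SCL-K-9 as an addition, not a substitute.
- *That half or more of any gain is lost and the result is biased against effective arms.* The table shows losses from 0% to 100% and one overstatement, depending on the course assumed. The document gives no course to choose between them.

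It is also fair to say that this is an additional economic analysis, and that Statistical analysis treats quality of life as exploratory.

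What survives is narrower. On the text as written, the months in which the prompts act have no scheduled quality-of-life value timed from randomisation.

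**Conclusion.** The point holds as a weakness of timing that is cheap to repair. Following the text, the cost-utility analysis would rest on KIDSCREEN-10 at one and two years from central-project enrolment, and a gain that appears early and fades before one year would be largely or wholly missed (0.875u true against 0 recovered in the example). The size is conditional: nil for a linear rise to month 12, 25% for a gain constant to month 24.

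The conclusion rests on the text giving the complete schedule, which Fig. 3 could contradict, and on linear interpolation between assessments. The figures in the table further assume a negligible lag between the two enrolments and no difference between arms at the start. The primary endpoint, its sample size and the comparison of arms on alcohol use are unaffected.

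**What to change.** - Add KIDSCREEN-10 to the online assessments at t1, t2, t3 and t4. If Fig. 3 already shows it there, bring the text under Secondary outcome measures into line with the figure.
- State the horizon of the cost-utility analysis, and compute QALYs by arm as the area under the curve from SP3 randomisation. Place the one- and two-year school values at their actual time since randomisation.
- Name in advance the conversion from KIDSCREEN-10 score to utility. If none is available, do not report cost per QALY, and rely on the cost-effectiveness ratio on study outcomes that the article already plans.

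The cost is 10 items at each of four existing online assessments, 10 × 4 = 40 item responses per participant. No extra contacts are needed, and t2 to t4 already carry vouchers. The downside is a slightly longer questionnaire. According to Trial status, recruitment had not begun when the article was written, so at that stage the change could have applied to every participant.

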### Sample size and power calculation

Two focus groups will be realised in study phase 2 with five participants each. *N* = 20 at-risk alcohol-consuming children and adolescents will be recruited for the pilot testing of the newly designed TIPs. For the RCT, *N* = 15,000 children and adolescents will be assessed for eligibility (ProHEAD school sample). The estimated number of eligible participants for the ProWISE-TIP trial based on current data on the prevalence of risky alcohol consumption is *n* = 3270 [51]. Criteria for the allocation of participants to the five individual ProHEAD trials are based on latest scientific evidence. However, this is the first time that the overall algorithm is applied on a consortium-wide basis simultaneously screening for various mental health problems. Therefore, an intermediate data analysis will be conducted following completion of 10% of the screening assessments (*N* = 1500) in order to determine the actual allocation ratio to the five ProHEAD trials and to adjust the screening algorithm if necessary. Based on prior research, we expect that the ProWISE-TIP intervention reaches a small effect size (f = 0.10) when compared to the ProWISE-only condition and a medium effect size (f = 0.25) when compared to the psychoeducation control group [33, 35]. Thus, a total sample size of *N* = 1076 (intention-to-treat) (*n* = 269 in each trial arm) are needed (power = 0.80; alpha = 0.05, two-tailed; f = 0.10) in order to show superiority of the ProWISE-TIP intervention.

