#### Primary outcome measure

For reasons of comparability, we chose to use the same primary outcome as in our previous study, testing the effectiveness of the original version of the web-based brief alcohol intervention without TIPs [24]. Therefore, the primary outcome is alcohol use in the past 30 days at nine-month follow-up as assessed by an index score for frequency and quantity of drinking and frequency of binge drinking calculated from the first three items of the Alcohol Use Disorders Identification Test (AUDIT-C) [41] adapted to assess drinking in the past 30 days. Frequency of alcohol consumption and frequency of having six drinks at one occasion (binge drinking) are assessed with response options ranging from 0 (never) to 4 (four or more times a week). The assessment of quantity of standard drinks consumed per typical drinking occasion (0 = one or two to 4 = ten or more) is supported by a graphical overview over units of alcoholic drinks defined as standard drinks. The AUDIT-C is validated in a sample of 14- to 18-year-old students in Germany [51].

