### Statistical analysis

Focus groups in study phase 1 will be evaluated by qualitative content analysis of data gained from the two focus groups. Details on study population will be provided by descriptive data analysis. In the RCT, intention to treat (ITT) analyses of primary data will be based on the available clinical data from all randomised participants after the nine-month follow-up. Missing data will be replaced by multiple imputations. For the primary endpoint, a mixed linear repeated measurement model (LMM) with the participant ID as random, group and time as fixed factor will be performed which is more robust against drop-outs than models without random factor [64] and uses the direct maximum likelihood as the statistical estimation procedure, which results in unbiased estimators under the missing-at-random-assumption [65]. We will use the closed test principle to evaluate differences between the means of groups. An additional analysis will be conducted on the per-protocol sample. The secondary endpoints alcohol-related problems, co-occurring substance use and help-seeking in those with transition to full-threshold alcohol use disorder, other mental health symptoms and quality of life will be examined in an exploratory manner with appropriate procedures, including subgroup analyses of gender of participants. Interim analyses will be performed after each wave of recruitment. Statistical analyses will be carried out with SPSS, Version 22 [66]. Associations between program usage patterns and reductions in alcohol use will be examined using latent class analysis (LCA) with Mplus, Version 5 [67].

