### Compliance / Rate of loss to follow-up

According to recent reports on follow-up rates in trials testing web-based alcohol interventions and text-message-based interventions, follow-up data for 80% of randomised individuals are expected at the three-month follow-up, 75% at the six-month follow-up and 70% at the nine-month follow-up (primary endpoint) in the four trial arms [19, 24, 33]. These follow-up rates seem feasible because of the recruitment setting (schools) and the use of incentives. Participants will receive online gift vouchers after completion of each program-specific assessment at the follow-ups at three (€10), six (€20) and nine (€25) months.

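### 269 per arm does not give the stated 80% power for ProWISE-TIP versus ProWISE only at nine months unless an unstated correlation of about 0.56 (complete data) or 0.72 (70% follow-up) is assumed

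*Protocol article*

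**What the plan says.** Under Sample size and power calculation, the protocol article expects that the ProWISE-TIP intervention "reaches a small effect size (f = 0.10) when compared to the ProWISE-only condition", and it expects "a medium effect size (f = 0.25) when compared to the psychoeducation control group". From these expectations it derives a total of 1076, labelled intention-to-treat, with the parameters "269 in each trial arm) are needed (power = 0.80; alpha = 0.05, two-tailed; f = 0.10) in order to show superiority". It names no test, no within-person correlation and no dropout allowance.

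Three other sections bear on the figure:

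- Primary outcome measure: "the primary outcome is alcohol use in the past 30 days at nine-month follow-up".
- Compliance / Rate of loss to follow-up: data are expected for "70% at the nine-month follow-up (primary endpoint) in the four trial arms".
- Statistical analysis: a linear mixed repeated-measures model estimated by maximum likelihood, multiple imputation, and a closed test for differences between group means.

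**The concern.** The smaller effect is tied to A versus C, and the sample-size sentence follows from it and speaks of superiority, so it reads as a power claim for that contrast. A two-arm comparison at d = 0.20 needs clearly more than 269 per arm, and the plan itself expects to lose 30% of participants by the primary endpoint.

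Whether the prompts add to the single-session intervention is one of the two questions that the Discussion says the four-arm design will answer. The comparison with psychoeducation (f = 0.25, d = 0.50) has over 99% power at either 269 or 188 per arm, so the shortfall falls on the added-value question. If the chance of detecting the planned effect is nearer one half than four fifths, a non-significant result could easily be misread as showing that prompts add nothing.

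**Working it through.** **Inputs.** From Sample size and power calculation: n = 269 per arm, four arms, two-sided alpha 0.05, power 0.80, f = 0.10 for A versus C. From Compliance / Rate of loss to follow-up: 70% at month nine, so 0.70 × 269 = 188 per arm. From Primary outcome measure: the endpoint is month nine. Not in the article, so assumed over a range: the correlation r between the month-nine score and baseline or earlier scores.

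**Step 1. What could have produced 1076?**

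- *Four-group omnibus F-test, no dropout.* Non-centrality is N·f² = 1076 × 0.01 = 10.76 with 3 and 1072 degrees of freedom; power is 79.3%. Reaching 80% in equal arms takes 1096 (274 per arm). This is near 1076 but not equal to it.
- *Two-group between-subject test averaged over four measurements, correlation 0.3.* Non-centrality is N·f²·m / [1 + (m − 1)·r] = 376 × 0.01 × 4 / 1.9 = 7.92; power is 80.1% at 188 per arm. Inflating for 30% loss gives 188 / 0.70 = 268.6, rounded up to 269, and 4 × 269 = 1076. This is an exact match, but the correlation of 0.3 is nowhere in the article.

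The first tests whether any of four means differ. The second tests a difference averaged over time points. Neither is A versus C at month nine.

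**Step 2. A versus C at month nine, no correlation gain.** d = 2f = 0.20. Required n per arm = 2 × (1.960 + 0.842)² / 0.20² = 393 (394 by exact t). Power is approximately Φ(d·√(n/2) − 1.960):

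- 269 per arm: 0.20 × √134.5 = 2.319, power 64.0% (exact t 63.9%)
- 188 per arm: 0.20 × √94 = 1.939, power 49.2% (exact t 49.0%)

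**Step 3. The same contrast with a correlation gain.** Adjustment reduces the standard deviation from 1 to √(1 − r²).

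| Assumed r | Power, 269 per arm | Power, 188 per arm |
|---|---|---|
| 0 | 64% | 49% |
| 0.3 | 68% | 53% |
| 0.5 | 76% | 61% |
| 0.7 | 90% | 77% |

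80% power requires 1 − r² = n / 393:

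- 269 per arm: r = √(1 − 269/393) = 0.56
- 188 per arm: r = √(1 − 188/393) = 0.72

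**Step 4. Effect detectable with 80% power, before any correlation gain.** d = 2.802 × √(2/n):

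- 269 per arm: d = 0.242, f about 0.12
- 188 per arm: d = 0.289, f about 0.14

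**The case against.** The strongest reply is that 1076 was calculated correctly, for a repeated-measures test that the article does not describe. The second candidate in the working reproduces 269 exactly. Apart from the correlation, its ingredients are in the article: a two-arm contrast at f = 0.10, four sub-project assessments (t1 to t4), 70% retention and a repeated-measures model. It would also explain the intention-to-treat label as meaning randomised rather than completing participants. This stands as far as it goes. A reader might infer that 1076 is simply an omnibus figure with no allowance for attrition; the article does not establish either statement. But the match does not rescue the power sentence. That calculation powers the average over time points, and if the four measurements are t1 to t4, the average includes baseline, where randomised arms should not differ. At the same r = 0.3, power at month nine with 188 per arm is about 53%.

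A second reply is that 64% and 49% belong to an unadjusted comparison of completers, whereas the plan uses a mixed model on all randomised participants. This is right, and the two figures must carry that label. A reader might take 49% as the power of the planned analysis; the article does not support that, because the gain depends on an unstated correlation. The gain is limited, however. A mixed model with an equal correlation between all measurements, the stated retention and baseline used gives about 53% at r = 0.3 and about 62% at r = 0.5. Under missing at random, imputation and maximum likelihood address bias; they recover information only as far as the correlated measurements allow.

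A reader might also infer that closed testing lowers the power further by a known amount. The article says only: "We will use the closed test principle to evaluate differences between the means of groups". It specifies neither the family of hypotheses nor an order, and gives no expected mean for the ProWISE-TA arm, so no figure can be attached. A fixed sequence is itself a closed test, and these details may properly sit in the full protocol or SAP.

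Finally, a condensed article may leave the name of the test to the full protocol. That is fair for the name alone. Here the article prints effect, alpha, power, sample size and retention together, and for the contrast to which it ties the effect they do not agree.

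**Conclusion.** The point holds in a conditional form. As printed, the sentence claims 80% power for A versus C at f = 0.10, and at the nine-month endpoint the design does not deliver this on the stated inputs. At the expected retention a plausible range is roughly 49% (unadjusted) to 61% (r = 0.5), and only a correlation of about 0.72 would restore 80%.

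The conclusion rests on reading f = 0.10 as the two-group value (d = 0.20), as the text assigns it; on month nine as the target time point; and on 70% retention in each arm. It does not depend on knowing how 1076 was obtained, which the article leaves open. The statement should be corrected because it misdescribes the power for a main question of the trial; the sample size itself need not change.

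**What to change.** In the sample-size paragraph, do one of the following for ProWISE-TIP versus ProWISE only at nine months:

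- restate the power, for example about 49% unadjusted to about 61% at an assumed r = 0.5 with 70% follow-up; or
- state the effect detectable with 80% power: f about 0.12 with complete data and about 0.14 at 70% follow-up, before any correlation gain.

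In either case, name the test behind N = 1076, the contrast and time point it powers, the correlation assumed and its source, and whether 269 per arm already includes the 30% loss.

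The cost is a few sentences and a less favourable stated power for this comparison. No extra participants are needed.
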